### 3.12.2. Additional analyses

N/A

### 3.12.3. Analysis population and missing data

N/A

## 3.13. Data monitoring

## 3.14. Safety/harms

N/A

## 3.15. Auditing

N/A

# 4. ETHICS AND DISSEMINATION

## 4.1. Research ethics approval

This study adhered to the principles outlined in the Declaration of Helsinki. The approval was granted by the Ethics Committee for Investigation of Aragon (CEICA).

## 4.2. Protocol amendments

Protocol changes or modifications to this observational study will be reported in ClinicalTrials.gov.

## 4.3. Informed consent process

All the patients will sign the informed consent specifically designed for this study.

## 4.4. Confidentiality

Sociodemographic, clinical, laboratory and follow-up data of each patient will be included in a database specifically designed for the study. All variables will be included in the online data collection platform Redcap (Research Electronic Data Capture).  Each patient will be assigned a number; their identity will not be revealed in any case. All shared information will be anonymized.

## 4.5. Declaration of interests

None of the principal investigators have relevant relationships to the contents of this study to disclose.

## 4.6. Access to data

Only principal investigators will have access to the trial dataset. No disclosure of contractual agreements limit such access for investigators.

## 4.7. Dissemination policy

### 4.7.1. Trial results

Trial results will be reported via publication.

### 4.7.2. Authorship

Authorship eligibility guidelines will be established  according to the number of patients included by each center.

### 4.7.3. Reproducible research

N/A

## 5.2. Funders

No funding.

## 5.3. Roles and responsibilities

### 5.3.1. Protocol contributors

**Index of microvascular resistance (IMR)-guided management of heart transplantation**

**IMR-Heart Transplant Study**

**PROTOCOL**

**SUMMARY**

| **Study title** | INDEX OF MICROVASCULAR RESISTANCE-GUIDED MANAGEMENT OF HEART TRANSPLANTATION |
| --- | --- |
| **Short Running Title** | IMR-HEART TRANSPLANT STUDY |
| **Investigators** | [name]  [name]  [name]  [name] |
| **Study aim** | Follow-up assessment of heart transplant patients based on IMR |
| **Hypothesis** | The index of microvascular resistance will serve to reduce the number of endomyocardial biopsies in transplant patients. |
| **Study design** | Multi-center, prospective, observational |
| **Inclusion criteria** | Heart transplant patients >18 years. |
| **Exclusion criteria** | Patients presenting with hemodynamic instability after HT, including cardiogenic shock or severe coagulopathy. Patients with acute cellular rejection before intracoronary physiological assessment. Patients with bronchial asthma or bronchopathy with a positive bronchodilation test, which contraindicates the use of adenosine. Patients with epicardial coronary lesions with a resting physiological index ≤0.89 or ≤0.80 at hyperemia. Patients unlikely to cooperate in the study or with inability or unwillingness to give informed consent. |
| **Primary endpoint** | Number of biopsies performed in the first year.  IMR in transplant patients, in the first three months and one year. |
| **Secondary endpoints** | Cardiovascular mortality and IMR.  Cardiac allograft vasculopathy and IMR.  Acute cellular rejection and IMR.  IMR variation, in the first two months and at one year.  Combined endpoint of ACR, heart failure, re-transplantation, cardiovascular mortality and IMR.  Immunosuppressive therapy and IMR. |
| **Data analysis** | Observational, analytical |
| **Follow-up** | 1 year and annually for five years |

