## 3.3. Interventions

### 3.3.1. Intervention description

Based on IMR results, patient clinical status and the other complementary tests:

- If the IMR is less than 15, the number of biopsies could be reduced or kept the same. No immunosuppressive therapy changes would be made.

- If the IMR is 15 or greater, number of biopsies would be performed as usual per protocol. Immunosuppressive therapy could be intensified or maintained the same.

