## 3.4. Outcomes

- The **primary outcome** of the study is to evaluate IMR values and number of EMB performed in the first year after HT: Depending on IMR values obtained in the first three months, clinical status and the other complementary tests the physician will be able to modify the number of biopsies established in each center protocol.If the IMR is less than 15, the number of biopsies could be reduced or kept the same. If the IMR is 15 or greater,number of biopsies would be performed as usual per protocol.

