**HYPOTHESIS**

Number of EMB performed in the first year post-HT could vary depending on IMR values. Low IMR values in the first three months could reduce the number of protocol EMB. Meanwhile, high IMR values would not modify the number of EMB performed, and could even contribute to intensify immunosuppressive therapy.

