***Biopsies and immunosuppressive therapy***

Based on IMR results:

- If the IMR is less than 15, the number of biopsies could be reduced or kept the same. No immunosuppressive therapy changes would be made.

- If the IMR is 15 or greater, immunosuppressive therapy could be intensified or maintained the same. Number of biopsies would be performed as usual per protocol.

Given the observational characteristics of the study, decisions regarding clinical patient management will depend on physician discretion considering patient clinical condition and other complementary tests.

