***Changes in EMB protocol based on coronary microvascular resistance***

- Each center will specify the number of annual biopsies performed based on IMR values obtained between the first two months after HT.

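### The primary biopsy count measures how far physicians take up the IMR rule; it cannot show that IMR identifies patients who can safely have fewer biopsies

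*Protocol*

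**What the plan says.** The hypothesis in the Protocol's SUMMARY table (under 5.3.1) is that "The index of microvascular resistance will serve to reduce the number of endomyocardial biopsies in transplant patients". The HYPOTHESIS section puts it more cautiously: "Low IMR values in the first three months could reduce the number of protocol EMB". The first primary endpoint in the SUMMARY table is "Number of biopsies performed in the first year", listed beside the IMR values.

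The management rule acts on that same count:

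- Below the cut-off (Biopsies and immunosuppressive therapy; also 3.3.1 and 3.4): "If the IMR is less than 15, the number of biopsies could be reduced or kept the same".
- At or above it (3.3.1): "If the IMR is 15 or greater, number of biopsies would be performed as usual per protocol".
- Section 3.4 makes the rule part of the primary outcome: "the physician will be able to modify the number of biopsies established in each center protocol".
- The section on changes in the EMB protocol adds: "Each center will specify the number of annual biopsies performed based on IMR values obtained between the first two months after HT".
- The section on biopsies and therapy ends with a discretion clause: "decisions regarding clinical patient management will depend on physician discretion considering patient clinical condition and other complementary tests".

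The Trial Summary describes a non-randomized, single-group design. The last sentence of INTRODUCTION AND RATIONALE gives the aim as finding out whether management can be changed safely on the strength of IMR. Rejection, mortality, vasculopathy and the combined endpoint are secondary, each related to IMR.

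**The concern.** The endpoint and the intervention are the same quantity. IMR can move the count in one direction only, and only in patients below 15. No rejection, graft or survival result enters the primary conclusion. If the IMR reading carried no information about rejection, physicians who used the permission would still produce fewer biopsies in the low group.

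A publication could therefore report that IMR serves to reduce biopsies, and readers would take this as support for doing fewer. The data would look the same whether IMR were useful, useless or harmful. No control group, managed without knowledge of IMR, is available to separate these explanations. Patients at 15 or above do not fill that role, because the rule fixes their schedule as usual.

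**Working it through.** **Step 1: what the rule permits.**

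| First IMR | Permitted change in EMB count | Patient outcome entering the primary conclusion |
|---|---|---|
| Below 15 | down, or none | none |
| 15 or above | none | none |

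Write the year-one count as: count = centre schedule + extra biopsies − cut. The rule links only the cut to IMR. If IMR is unrelated to rejection, the schedule and the extra biopsies have the same distribution in both groups. The expected difference (low minus high) is then −q × r, where q is the share of low-IMR patients whose schedule is cut and r is the number of biopsies removed. The accuracy of IMR appears nowhere in this expression.

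**Step 2: inputs.** From the Protocol: 100 patients analysed (Trial Summary, 3.7), usually up to 5 biopsies in year one (2.1), up to 20% with cellular rejection in year one (INTRODUCTION AND RATIONALE), two-sided 0.05 (3.12.1). The target of 100 rests on centre volume, with no effect size, SD or power, so there is no stated power to reproduce.

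Assumed, because the Protocol does not give them: 30%, 50% or 70% of patients below 15; q from 0 to 1; r of 1 or 2; and a Mann-Whitney comparison of low with high IMR, taken from the general methods list.

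**Step 3: simulation with IMR independent of rejection.** Model A: schedule of 4 to 6, plus one extra biopsy in 20% of patients in both groups; 2,000 runs per cell. Model B: eight centres scheduling 4 or 5, plus Poisson(0.5) for-cause biopsies in both groups; 1,500 runs per cell. The entries are the share of trials with p<0.05 and a lower mean in the low-IMR group. Ranges run over the three IMR splits.

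| Uptake q, cut r | Model A | Model B |
|---|---|---|
| 0 | 2.5-3.0% | 2.1-2.8% |
| 0.25, one fewer | 19-21% | 20-28% |
| 0.50, one fewer | 58-65% | 70-76% |
| 0.75, one fewer | 91-95% | 96-99% |
| 0.50, two fewer | 94-98% | 96-98% |

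**Step 4: hand check of Model A**, 50 per group, normal approximation.

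- Variance of the uncut count: 2/3 + 0.20 × 0.80 = 0.827, so SD 0.91.
- At q = 0.5, r = 1 the difference is 0.5. Partial uptake adds 0.5 × 0.5 = 0.25 to the low group's variance, giving 1.077.
- SE = √(0.827/50 + 1.077/50) = 0.195; power ≈ Φ(0.5/0.195 − 1.96) = 73%. The simulated Mann-Whitney figure at this split is 65%; the rank test is somewhat less powerful with so many ties.
- At q = 1, r = 1: SE = √(2 × 0.827/50) = 0.182; power ≈ Φ(1/0.182 − 1.96), above 99.9%, against a simulated 100%.

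**Step 5: does the secondary ACR analysis fill the gap?** Not fully. INTRODUCTION AND RATIONALE says that most cellular rejection is silent and is found by biopsy. If low-IMR patients have fewer biopsies, fewer of their rejections are found. The ACR-by-IMR comparison is then biased towards making IMR look protective. The combined endpoint contains ACR and inherits the problem.

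**Step 6: how precise could a safety estimate be?** The reduced-biopsy subset numbers 100 × (share below 15) × q. Over 30-70% and 0.25-0.75 this runs from 7.5 to 52.5, so roughly 8 to 52 patients. With zero events the exact two-sided 95% upper limit is 1 − 0.025^(1/n): 37% at n = 8, 14% at n = 25, 7% at n = 52.

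**The case against.** A reader might infer that the Protocol orders physicians to cut biopsies below 15, so that the hypothesis confirms itself. The text does not support this. Every statement of the rule allows the number to stay the same, and the discretion clause means that a physician who changes nothing complies fully. The simulations agree: with no uptake, success occurs at the nominal rate.

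A reader might also infer that a low-versus-high IMR test of the count is planned. None is named; the methods sections list generic tests, and the comparison may be fixed in a SAP that is not shown. The percentages above illustrate how such a test would behave and do not predict this study's result.

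The best defence is that uptake is a legitimate question. The introduction says that no study has examined the effect of IMR on management, and the HYPOTHESIS section says only that the count could vary with IMR. Rejection, mortality and vasculopathy are examined as secondary endpoints, so the information content of IMR is not ignored.

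This defence stands as far as it goes. It supports calling the count a measure of management impact. It does not support the wording in the SUMMARY table, and it does not connect the primary result to the stated aim of safe modification. The secondary ACR analysis cannot fully supply that link, for the reason in Step 5.

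**Conclusion.** The concern holds in limited form. The primary hypothesis is judged on a count that the Protocol's own rule allows to fall only below 15, in a design without a control. A lower count is evidence of uptake. It is not evidence that IMR is valid or that fewer biopsies are safe.

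That conclusion follows from the text and needs no simulation. Its size depends wholly on assumed uptake: about 2-3% nominal success with none, roughly 20-30% at one quarter, 58-76% at one half, and over 90% at three quarters, each with one biopsy fewer and an uninformative IMR. A SAP could choose the test but could not make this count informative about IMR, because the hypothesis, endpoint and rule are all fixed in the Protocol.

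**What to change.** In the SUMMARY table, the HYPOTHESIS section and section 3.4:

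1. Restate the biopsy count as a descriptive measure of management uptake: EMBs performed against the number in the centre's own schedule, and the proportion of patients with IMR below 15 whose schedule was reduced and by how many, with 95% CI.
2. State that this result alone supports no claim that IMR is valid or that a reduction is safe.
3. Make any safety statement separately, with its CI, from outcomes already collected whose detection does not depend on the number of surveillance biopsies: heart failure, re-transplantation and cardiovascular mortality.
4. Report ACR beside the number of biopsies performed in each IMR group. Do not make the claim conditional on the combined endpoint, because its ACR component becomes easier to pass as biopsies are cut.

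The cost is wording, plus recording each centre's scheduled number, which section 3.4 already presupposes. No extra patients or procedures are needed. The primary claim becomes more modest. The safety estimate will be imprecise (Step 6) and comes from patients selected by their physicians, so the report should say so.

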# 2. INTRODUCTION

## 2.1. Background and rationale

Acute allograft rejection (AAR) is an important cause of morbi-mortality  after heart transplant (HT), particularly within the first year. Advances in immunosuppression, donor heart evaluation, surgical techniques, and post-transplantation care have led to a gradual reduction in AAR and improved survival after HT over time. Endomyocardial biopsy (EMB) is the gold standard method to guide post-HT treatment, as it represents the best tool to identify rejection in orthotopic HT. However, it is usually repeated up to 5 times during the first year - with some variations depending on each center protocol - and it is potentially associated with serious complications.

Several studies have presented the association between AAR, micro-vasculopathy and cardiac allograft epicardial vasculopathy (CAV).  Index of microcirculatory resistance (IMR) measured early after heart transplantation has been significantly associated with the risk of acute cellular rejection (ACR), and patients with IMR≥15 have higher risk of AAR during 2 years follow-up.

The aim of our study is to evaluate if the use of IMR measured at baseline may be useful in guiding care of patients after HT.

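### The primary endpoint is a raw count of all biopsies, so a lower count at IMR below 15 cannot by itself be attributed to IMR guidance

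*Protocol*

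**What the plan says.** Every statement of the primary endpoint is a count of biopsies performed. The Primary endpoint row of the SUMMARY table (section 5.3.1) has "Number of biopsies performed in the first year". Section 2.2, section 3.4 and the ENDPOINTS text say the same in substance. None separates scheduled biopsies from those done for clinical reasons or to check the response after a rejection episode.

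The text on what IMR can change is narrower. The HYPOTHESIS section states "Low IMR values in the first three months could reduce the number of protocol EMB". Section 3.4 says that, depending on IMR and other findings, "the physician will be able to modify the number of biopsies established in each center protocol".

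The Hypothesis row of the SUMMARY table is broader: "The index of microvascular resistance will serve to reduce the number of endomyocardial biopsies in transplant patients". The opening sentence of the HYPOTHESIS section is also not limited to protocol biopsies.

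On schedules, section 2.1 says of EMB that "it is usually repeated up to 5 times during the first year", "with some variations depending on each center protocol". The section on changes in the EMB protocol adds: "Each center will specify the number of annual biopsies performed based on IMR values obtained between the first two months after HT". It asks neither for the centre's standard schedule nor for the reason for each biopsy. The STUDY VARIABLES table has no biopsy row.

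Section 1 describes a non-randomized, single-group study. Section 3.12.1 lists unadjusted two-group tests for continuous variables and names Cox adjustment only for clinical events.

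**The concern.** The natural reading of the result will be a comparison of biopsy counts between patients with IMR below 15 and those at 15 or above. If the low group has fewer, this will be taken as biopsies spared by IMR.

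The same pattern can arise because IMR is prognostic. Section 2.1 says that patients at or above 15 have a higher risk of rejection. Rejection and clinical deterioration can prompt additional biopsies, so the high group may accumulate more of them whether or not any physician uses IMR. With no comparator, nothing else in the design separates the two explanations.

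The opposite error is also possible. If low-IMR patients with a thinned schedule have extra for-cause biopsies, these cancel the omitted ones in the total, and a real change in scheduled biopsies disappears from view.

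**Working it through.** The protocol states no expected difference in biopsy counts, so there is no figure of its own to reproduce. The steps below size the problem.

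**Inputs from the protocol**
- Acute cellular rejection (ACR) in year one: up to 20% (INTRODUCTION AND RATIONALE).
- Higher rejection risk at IMR 15 or above, size not given (section 2.1).
- 100 patients, eight centres (section 3.7); two-sided 0.05 (section 3.12.1).

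**Assumptions**
- Half the patients have IMR 15 or above.
- The ACR risk ratio, high versus low IMR, is 2 to 3.
- Each episode brings 1 to 3 extra biopsies.
- A 10% ACR rate is used as a lower case, because patients with ACR before the physiological study are excluded.

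**Step 1: difference with no guidance effect**

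Low-group risk = overall risk / (0.5 × RR + 0.5). Spurious difference = (RR − 1) × low-group risk × extra biopsies per episode.

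| Overall ACR | RR | Low IMR | High IMR | Difference, 1 extra | Difference, 3 extra |
|---|---|---|---|---|---|
| 20% | 2 | 0.20/1.5 = 13.3% | 26.7% | 0.13 | 0.40 |
| 20% | 3 | 0.20/2 = 10% | 30% | 0.20 | 0.60 |
| 10% | 2 | 0.10/1.5 = 6.7% | 13.3% | 0.07 | 0.20 |
| 10% | 3 | 0.10/2 = 5% | 15% | 0.10 | 0.30 |

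The range is 0.07 to 0.60 biopsies per patient. For scale, a real saving of one biopsy in half of the low-IMR patients is 0.5 × 1 = 0.5.

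**Step 2: how often this reaches p < 0.05**

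Trials of 100 patients at eight centres were simulated, 3,000 per scenario, using the protocol's t test and Mann-Whitney test. Five biopsies were scheduled everywhere, there was no guidance effect, and extra biopsies per ACR averaged 1 to 3.

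- ACR 20% in both groups (average of 2 extra only): about 5%, as it should be.
- ACR 15% low versus 25% high: 14% to 20% of trials.
- ACR 10% low versus 30% high: 41% to 69% of trials.

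The difference in scheduled biopsies alone was 0.00 throughout. These rates assume identical schedules and no other variation in the count; more variation would lower them without removing the shift in Step 1.

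**Step 3: centre schedules**

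ACR was set equal in both groups, with no guidance effect and an assumed schedule for each centre.

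- Schedules of 3 to 8, same IMR mix at every centre: about 5%. This is noise, not bias.
- Same schedules, IMR mix varying by centre (SD 0.5 to 1.0 on the logit scale): 10% to 23%.
- Schedules of 4 to 6, same variation in mix: 8% to 19%.

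The error went in either direction.

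**Step 4: hiding a real change**

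One scheduled biopsy is truly dropped for each low-IMR patient. Power of the t test on the total count:

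| Extra for-cause biopsies per low-IMR patient | Uniform schedule | Schedules of 3 to 8 |
|---|---|---|
| 0 | 99.7% | 74% |
| 0.5 | 59% | 26% |
| 1.0 | 5% | 5% |

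The Mann-Whitney test does better at 0.5 extra with a uniform schedule (95%), but not with varying schedules (32%) or at 1.0 extra (12% and 6%). The scheduled-only difference stays at about −1.0 in every case.

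**The case against.** **The hypothesis is not only about protocol biopsies.** The SUMMARY table words it for biopsies in general, and a total count matches that wording. This stands: the narrower reading rests on the HYPOTHESIS section and section 3.4. The attribution problem remains under the broader wording, because that too says IMR will serve to bring about the reduction.

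**The for-cause excess is not documented.** The INTRODUCTION AND RATIONALE says that most ACR is asymptomatic and found by biopsy. Section 2.1 refers to rejection over two years and gives no size. Prior ACR is excluded, and immunosuppression may be intensified at high IMR, which could narrow the gap. This also stands. The high group may, not must, have more such biopsies, and the sizes above are illustrative.

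**Total biopsies are a legitimate measure of patient burden.** If a thinner schedule provokes for-cause biopsies, netting them off is right for burden. A scheduled-only count would hide that rebound and would partly measure uptake of the IMR rule. Hence both counts are needed.

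**An observational single-group study limits attribution under any endpoint.** True, and a reason not to treat this as fatal. It does not justify a count that mixes the biopsies IMR can change with those driven by prognosis.

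**Conclusion.** The point holds with limits. The endpoint counts all biopsies, guidance acts on the scheduled ones, and the protocol neither separates them nor sets the count against the centre's schedule. A lower raw count at IMR below 15 therefore cannot be credited to guidance. Under the stated assumptions, prognosis alone could produce 0.07 to 0.60 biopsies per patient; only the 20% ACR ceiling and the direction of risk come from the protocol.

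A reader might infer three stronger things that the document does not support:
- That the raw count answers none of the stated hypotheses. It does match the SUMMARY wording as a description of burden.
- That differing centre schedules by themselves create a false reduction. They add noise, and they bias the comparison only if IMR mix differs by centre or the count is read against an outside norm.
- That the database lacks an indication field. The form is not shown; the protocol simply does not call for one.

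This should be fixed, but it does not invalidate the study. It is not a detail to leave to an analysis plan, because no later model can recover an indication or a schedule that was not recorded.

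**What to change.** 1. Reconcile the wordings of the hypothesis in the SUMMARY table, the HYPOTHESIS section and section 3.4, stating whether the claim concerns scheduled biopsies, total biopsies or both.
2. Record the indication of each EMB: scheduled, for-cause or post-rejection control.
3. Document each centre's standard schedule as it stood before IMR guidance. Section 1 shows that enrolment began in March 2024, so this may have to be taken from existing centre protocols.
4. Base the claim of reduction on scheduled EMBs performed after the IMR study relative to the number the patient's own centre schedules for the same period, compared within centre or adjusted for centre.
5. Always report total EMBs and for-cause or control EMBs by IMR group beside it, so that any rebound is visible.

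The cost is revised endpoint wording, one field per biopsy (if not already collected) and one schedule form for each of eight centres. Recording these items changes no patient's care. The headline reduction may become smaller (if for-cause biopsies in the high group were inflating it) or larger (if they were masking it in the low group).

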## 3.12. Statistical methods

### 3.12.1. Outcomes

The characteristics of the study population will be summarized through standard descriptive statistics. Continuous variables will be expressed as mean (± standard deviation) or median [interquartile range (IQR)], as appropriate. Discrete variables will be presented as absolute numbers and percentages. For the comparison of means, the Student's t test for independent measures or the non-parametric Mann-Whitney U test (in the case of dichotomous qualitative variables) and the ANOVA or non-parametric Kruskal test will be used as a hypothesis test. Wallis (in the case of non-dichotomous qualitative variables). For the bivariate analysis of the qualitative variables, the Chi-square test or Fisher's exact test will be used. Events will be compared between groups by using Kaplan-Meier curves. Cox regression analysis will be performed to adjust for confounding factors and to evaluate independent predictors of clinical events. A two-tailed p-value of 0.05 will be considered statistically significant. All statistical analyses will be performed by SPSS software version 20.

In 2023, around 325 heart transplants were performed in Spain (3). Given a median of 10-15 HT per center and considering that eight centers that routinely perform invasive coronary physiology are participating, data will be analyzed when 100 patients have completed first year follow-up.

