Various studies have demonstrated the association between ACR, microvascular dysfunction (MVD) and cardiac allograft vasculopathy (CAV) (8). IMR is a quantitative and specific index for coronary microcirculation (9-10).  An increased IMR in the graft has been associated with higher all-cause mortality and adverse cardiac events regardless of epicardial vasculopathy (11). Several IMR cut-off (from 15 to >25) have been associated with ACR within the first year after HT. Patients in whom IMR decreases or does not change one year after HT have a higher event-free rate than those patients in whom the IMR increases (12-13). However, no study has evaluated IMR impact on post-HT management. In presence of a low IMR value, EMB could be performed less frequently; on the contrary, if the IMR value is high, immunosuppression therapy could be modified by an earlier administration of mTor-inhibiting drugs or prescribing calcium antagonists, which are known to improve microvascular function.

Our aim will be to assess if post-HT patient management may be safely modified based on IMR value.

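### The primary one-year biopsy count has no rule for patients who die, are re-transplanted or leave before month 12, and the resulting bias can go either way

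*Protocol*

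**What the plan says.** The primary outcome in section 3.4 is to "evaluate IMR values and number of EMB performed in the first year after HT"; the summary table in section 5.3.1 shortens the biopsy part to "Number of biopsies performed in the first year". Sections 2.2 and ENDPOINTS agree. None of them attaches a denominator, a period at risk or a rule for follow-up that ends early.

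The direction hoped for is stated twice. The summary's hypothesis is "The index of microvascular resistance will serve to reduce the number of endomyocardial biopsies in transplant patients". The HYPOTHESIS section splits it by group: "Low IMR values in the first three months could reduce the number of protocol EMB", while "high IMR values would not modify the number of EMB performed".

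For comparing means between two groups, section 3.12.1 lists "the Student's t test for independent measures or the non-parametric Mann-Whitney U test". Kaplan-Meier and Cox methods are named for clinical events only. Section 3.12.3, "Analysis population and missing data", contains only N/A. Sections 3.7 and 3.12.1 say that data are analysed once 100 patients have finished one year of follow-up.

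The introduction calls rejection the main cause of death and re-transplantation, above all in the first year, and adds: "An increased IMR in the graft has been associated with higher all-cause mortality and adverse cardiac events regardless of epicardial vasculopathy". Re-transplantation and cardiovascular death are components of the combined endpoint.

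**The concern.** A count over a fixed year is comparable between patients only if each could have been biopsied for the whole year. A patient who dies at month 4 has a low count because observation stopped, not because IMR spared a biopsy. The protocol anticipates such events and expects them to vary with IMR, the variable that defines the groups.

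The protocol also wants to know whether management can be changed safely on the basis of IMR. If follow-up cut short by death can lower the biopsy count, the primary result cannot be read without knowing who died, and when.

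**Working it through.** **What can be reproduced.** The only planning figure is the 100 patients. Eight centres at 10-15 transplants a year give 8 × 10 = 80 to 8 × 15 = 120 per year, so 100 is a feasibility figure. No effect size, SD, mortality rate or biopsy schedule is given, apart from the remark in section 2.1 that biopsy is usually repeated up to 5 times in the first year. Everything below is therefore illustrative.

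**Check 1: low versus high IMR, no true effect on biopsies.** Assumptions: IMR measured at month 2; k = 2, 3 or 4 biopsies remaining, evenly spaced to month 12; constant hazard after month 2 giving death risk p by month 12. A biopsy due at month t is done with probability (1 − p)^((t − 2)/10), so the expected count is the sum of these terms. For k = 2 (months 7 and 12) and p = 5%: 0.95^0.5 + 0.95 = 1.925. For p = 15%: 0.85^0.5 + 0.85 = 1.772. The difference is 0.153.

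| Deaths, low v high IMR | Low minus high, k = 2 | k = 3 | k = 4 |
|---|---|---|---|
| 2% v 5% | +0.05 | +0.06 | +0.08 |
| 5% v 15% | +0.15 | +0.20 | +0.26 |
| 5% v 20% | +0.23 | +0.31 | +0.39 |
| 10% v 0% | −0.15 | −0.20 | −0.25 |

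The hypothesis predicts a negative difference. The first three rows follow the ordering in the introduction (more deaths at high IMR) and work against it. Only the last row, the reverse ordering, produces a false reduction.

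With an assumed 50 patients per group and SD 1, the standard error is √(1/50 + 1/50) = 0.20. The bias is then 0.2-0.4 standard errors for 2% v 5%, 0.8-1.3 for 5% v 15%, and up to 1.9 for 5% v 20%.

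**Check 2: against a fixed centre schedule of 5 biopsies.** Assumptions: a share q of patients has follow-up cut short at a time uniform over months 2-12. A biopsy due at month t > 2 is lost to such a patient with probability (t − 2)/10; earlier biopsies are not lost. The mean raw count is 5 − q × loss. The mean time at risk is 1 − q × 5/12 years, and dividing the first by the second gives the rate per person-year.

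| Schedule (months) | Loss per truncated patient | Fall in raw mean, q = 2% to 15% | Rate per person-year (true 5) |
|---|---|---|---|
| Even: 2.4, 4.8, 7.2, 9.6, 12 | 2.6 | 0.05 to 0.39 | 4.99 to 4.92 |
| Intermediate: 1, 2, 4, 7, 12 | 1.7 | 0.03 to 0.26 | 5.01 to 5.06 |
| Front-loaded: 0.5, 1, 2, 4, 8 | 0.8 | 0.02 to 0.12 | 5.03 to 5.21 |

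The raw mean falls in every case, by 0.3% to 7.8%, with no change in practice. A simple rate removes most of this for the first two schedules but overshoots when biopsies are front-loaded.

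In this model, 2% truncation at low IMR and 10% at high IMR gives a between-group bias of 0.08 × loss = +0.06 to +0.21. If the low-IMR group truly has 20% fewer biopsies (a difference of −1.0), the raw counts show about −0.93 to −0.78.

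**Completers-only reading.** If the 100 are restricted to patients who finish the year, no count is truncated. But the set is then selected on survival, which the protocol expects to depend on IMR.

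**The case against.** The strongest reply is that the protocol never says a patient who dies early keeps a short count. The analysis trigger can be read as defining a completers set, and the list of tests is generic: neither the t test nor the Mann-Whitney test is assigned by name to the biopsy count, and IMR below 15 versus 15 or more is not declared the primary test. All of this stands. It does not remove the problem, because truncation and survivor selection are both biases and the protocol does not choose between them.

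A reader might infer that early deaths systematically produce the result the study hopes for. The documents do not support this. By the introduction's own premise, mortality is higher at high IMR, so the low-versus-high comparison is biased against the hypothesis. The bias is always favourable only in a comparison with the planned schedule.

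The size may also be small. Only patients who reach the IMR study, at one to three months, contribute, and those with haemodynamic instability or earlier cellular rejection are excluded. No document figure supports a mortality gap of 10 points or more.

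Finally, the choice of count model is usual SAP content. That is fair, but section 3.12.3 does not defer the matter; it declares it not applicable.

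**Conclusion.** The point holds as a gap in the definition of the primary endpoint whose bias has no fixed sign. The count is unqualified, the listed methods that fit it ignore time at risk, and the section where a rule belongs says N/A although the protocol expects the events that make one necessary.

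The plausible size runs from negligible (0.05-0.08 biopsies at 2% v 5% deaths) to about one standard error (0.15-0.26 at 5% v 15%), given the assumed mortality, spacing, SD of 1 and equal groups. Even spacing gives the largest loss of the three schedules tried. The change should be made because the endpoint is primary and the repair is cheap, not because a large distortion has been shown.

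**What to change.** Replace N/A in section 3.12.3 with the following:

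- **Analysis set:** all patients with a baseline IMR, whether or not they complete the year.
- **Count:** biopsies from the IMR measurement to the earliest of death, re-transplantation, withdrawal or month 12. Biopsies before the measurement cannot have been influenced by it.
- **Model:** Poisson or negative binomial regression with robust standard errors comparing IMR groups. The offset is the log of the biopsies due under the centre's usual schedule while the patient is alive with the original graft. With no effect of IMR, the expected count equals the number due in both groups, so the ratio is 1 whatever the pattern of deaths in the checks above. Log person-time with a schedule-period term is an alternative; person-time alone is not enough if biopsies are front-loaded.
- **Reporting:** deaths and re-transplantations by IMR group beside the primary result.

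The cost is protocol wording and one added data item, each centre's planned biopsy schedule. Dates of death and re-transplantation are already needed for the Kaplan-Meier and Cox analyses. A ratio is slightly less direct to read than a count, so the raw counts can still be shown descriptively.
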